Considering a type of implicit learning, motor priming has been used in neurorehabilitation to facilitate motor learning [22, 26]. The priming theory presumes that when the brain is activated using an intervention delivered prior to the motor learning intervention, it will become more responsive to motor training due to increased neural activity. This “therapeutic window” may result from the modulation of long-term potentiation or long-term depression, such as mechanisms [22, 27, 28]. Movement-based priming, using repetitive or continuous, unilateral or bilateral movements, is an important method of priming the motor cortex in neurorehabilitation [22].

This protocol describes a single-blinded, randomized clinical trial designed to determine whether AE, as a form of movement-based priming, has an effect on the outcomes of m-CIMT, specifically the recovery of the skill of paretic upper limb in persons with chronic stroke. We hypothesize that AE will potentiate m-CIMT, resulting in improved manual dexterity in people in the chronic phase poststroke.

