## Methods

This study is a randomized, single-blinded, intention-to-treat controlled clinical trial in which 78 participants of both genders in a chronic stage poststroke will be randomized into two groups of 39 participants. One group will receive AE combined with m-CIMT, and the other group will perform stretching exercises combined with m-CIMT. The eligibility criteria are presented in Table 1.

**Table 1 Tab1:** Eligibility criteria

Inclusion criteria	
• Stroke resulting in hemiparesis at least six months prior (chronic) • Do not a present lesion in the two hemispheres • Clinical diagnosis of ischemic or hemorrhagic stroke • ≥ 35 and ≤ 80 years old • Participants must present a minimum active movement of 45° of shoulder flexion or abduction, 20° of elbow extension, 10° of wrist extension, 10° of abduction or extension of the thumb, and 10° extension in at least two fingers (metacarpophalangeal and interphalangeal joints) and thumb • Participants must present the ability to pick up a towel using any grip [28] • Participants must present asymmetric of upper extremity, ≤ 2.5 in the Motor Activity Log (MAL) Quantity Scale [10] • Participants must have the ability to remain seated without trunk and arm support for 1 min [29]	
Exclusion criteria	
• Upper limb movement deficits attributable to no stroke pathology	
• Clear signs of dementia or cognitive disorder, indicated in the Mini- Mental State Examination (scores based in years of education, below 13 for illiterate individuals, 18 for individuals with 1 to 7 years of the primary school and 26 for individuals over eight years after primary school) [30, 31] • Individuals with lesion in cerebellar	
• The individuals are smokers, alcohol, or users of illicit drugs at the time of evaluation • Individuals with structural alterations in the cardiovascular and respiratory systems that will contraindicate the aerobic exercise • Individuals with uncorrected auditory and visual deficits • Individuals who present any electrocardiogram alteration or not the cardiorespiratory stress test • Individuals with historical diseases or osteomioarticular alterations • Individuals with body mass index > 28 • Individuals with uncontrolled diabetes mellitus or hypertension, comprehension aphasia, apraxia	

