### Statistical analysis

Demographic characteristics, such as weight, height and body mass index, will be presented as the mean and standard deviation. Median, maximum and minimum values will be used to describe poststroke time and UE-FMA score.

For all dependent variables, normality (Kolmogorov-Smirnov) and homogeneity (Levene) tests will be applied. If the variables present a normal and homogeneous distribution, then two-way analysis of variance with repeated measurements and Bonferroni’s correction will be used to examine the effect of group-by-evaluation time interaction, group (AE + m-CIMT and Stretching + m-CIMT), and evaluation time (baseline, 3, 30 and 90 days after the intervention). To protect against Type I error, Bonferroni’s correction will be used. Thus, each of the 10 planned comparisons will have to achieve *p* = 0.005 for statistical significance. The partial eta squared (η^2^) will be used to determine the effect size of the intervention. The mean difference from pre- and post-interventions and the corresponding 95% confidence interval (95% CI) will be calculated for each group (EA + m-CIMT and Stretching + m-CIMT) in order to estimate the effect of the intervention.

Otherwise, the Friedman test (*p* < 0.05) will be used followed by the Wilcoxon test with Bonferroni’s adjustment (*p* < 0.008) to compare evaluation time for each group baseline, 3 days, 30 days, 90 days after the end of treatment. The Mann-Whitney test with Bonferroni’s adjustment (*p* < 0.012) will be used to compare the groups in each time evaluation (EA + m-CIMT and Stretching + m-CIMT).

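### The effect of the intervention is defined as each arm's own pre-post change; neither branch names a between-group difference with a confidence interval, and the nonparametric branch does not test differential change

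*Protocol article*

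**What the plan says.** The Background frames a between-group question: whether aerobic exercise (AE) "has an effect on the outcomes of m-CIMT". The hypothesis follows: "We hypothesize that AE will potentiate m-CIMT, resulting in improved manual dexterity in people in the chronic phase poststroke". According to the section on m-CIMT, both arms get the same programme, 3 hours a day for 10 days (30 hours), starting 10 minutes after AE or stretching.

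The Statistical analysis section has two branches.

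- **Data normal and homogeneous.** A two-way repeated-measures ANOVA is used "to examine the effect of group-by-evaluation time interaction", and also the group and time main effects. Baseline is one of the four levels of time. Partial eta squared serves as the effect size. Then the pre-post mean difference and its 95% CI "will be calculated for each group (EA + m-CIMT and Stretching + m-CIMT) in order to estimate the effect of the intervention".
- **Otherwise.** Friedman and then Wilcoxon tests are run within each group. The Mann-Whitney test "will be used to compare the groups in each time evaluation (EA + m-CIMT and Stretching + m-CIMT", with a Bonferroni threshold. No effect estimate is named in this branch.

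**The concern.** The quantity given the role of effect estimate is not the one the trial was randomised to estimate. A patient in the AE arm may improve because of 30 hours of m-CIMT, because of repeated testing, or with the passage of time, whether or not AE contributes anything. An interval around that improvement, reported as the effect of the intervention, would normally look favourable even if priming does nothing.

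The second problem lies in the fallback branch. If an outcome fails the normality or homogeneity check, the interaction test disappears. What remains are tests of change inside each arm and tests of raw levels between arms at single visits. No test asks whether the arms changed by different amounts.

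This branch could well apply to the primary outcomes. The MAL runs from 0 to 5, and entry requires a score of at most "2.5 in the Motor Activity Log (MAL) Quantity Scale". The Nine-Hole Peg Test is stopped at 180 s, and non-completers are scored in pegs per second instead.

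**Working it through.** **1. The plan's own figures.** The thresholds are Bonferroni values: 0.05/10 = 0.005, 0.05/6 = 0.0083 (stated as 0.008) and 0.05/4 = 0.0125 (stated as 0.012). They reproduce. The issue is which quantity is estimated.

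**2. What each change contains.** Let M be what both arms share (m-CIMT, practice, time), A the contribution of AE and S that of stretching.

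- AE arm, pre-post change: M + A
- Stretching arm, pre-post change: M + S
- Difference between arms: A − S

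Only the third line is free of M. The plan attaches its 95% CI to the first two.

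**3. How misleading the within-arm interval can be.** The article gives no SD or correlation, so these inputs are assumed: 31 evaluable per arm (39 × 0.8 = 31.2), normal data with SD 1, equal correlation ρ between visits, a gain of 0.5 SD in both arms, and no priming effect. There were 2000 simulated trials per setting. The SD of change is √(2(1−ρ)), so the noncentrality of the within-arm test is 0.5 × √31 / √(2(1−ρ)).

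| | ρ = 0.5 | ρ = 0.7 | ρ = 0.8 |
|---|---|---|---|
| Noncentrality | 2.78 | 3.59 | 4.40 |
| AE arm's CI excludes zero (simulated) | 76% | 94% | 99% |
| Only one arm significant (simulated) | 36% | 12% | 2% |

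The last row agrees with 2p(1−p), where p is the unrounded simulated share in the row above: 2 × 0.757 × 0.243 = 0.37, 2 × 0.940 × 0.060 = 0.11 and 2 × 0.992 × 0.008 = 0.02. Under the same null, the planned interaction test rejects in 5–6% of trials and Mann-Whitney at 0.05 in 4–5%. Both are therefore valid tests. The fault lies in the estimate.

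**4. What the fallback branch gives up.** Relative to a raw comparison at one visit (variance 1), a comparison of change has variance 2(1−ρ) = 1.0, 0.6, 0.4 at ρ = 0.5, 0.7, 0.8. A baseline-adjusted comparison has 1−ρ² = 0.75, 0.51, 0.36, so its standard error is 0.87, 0.71 or 0.60 times the raw one. Simulated power with a true priming effect of 0.5 SD at every post-treatment visit, other inputs as above:

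| Test | ρ = 0.5 | ρ = 0.7 | ρ = 0.8 |
|---|---|---|---|
| Mann-Whitney, raw 3-day score, 0.05 | 48% | 48% | 47% |
| Mann-Whitney, raw 3-day score, 0.012 | 26% | 25% | 24% |
| Mann-Whitney, change to 3 days, 0.05 | 47% | 68% | 85% |
| Baseline-adjusted 3-day comparison, 0.05 | 62% | 77% | 90% |
| Planned group-by-time interaction, 0.05 | 50% | 74% | 91% |

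The like-for-like comparison is at 0.05, between the first row and the third or fourth. The drop to the second row comes from the multiplicity threshold, not from ignoring baseline. The interaction row draws on all four visits and the other rows on at most two. The simulated data are normal, so the table shows how baseline information helps, not the exact power for skewed scores.

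**The case against.** The strongest reply is that the parametric branch already tests the right thing. Baseline is a level of the time factor, so the group-by-time interaction asks whether the arms change differently. Its power is close to that of a baseline-adjusted test at ρ = 0.7 to 0.8. That stands. A reader might infer that the plan's group tests in general ignore baseline; only the Mann-Whitney tests do. The ANOVA group main effect does average baseline in, so it carries (0 + δ + δ + δ)/4 = 0.75δ of a constant post-treatment effect δ. It is not, however, the term that addresses priming.

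It can also be said that the plan is not without an effect measure. Partial eta squared is named, and in the parametric branch a reader could combine the two arms' mean changes and intervals into an approximate difference. So it would be too strong to say that no estimate exists. But partial eta squared is unsigned, is not in outcome units, has no stated interval and is not tied to a named model term. A difference that readers must work out themselves is not the plan's estimate.

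A reader might further infer that priming will be declared when one arm is significant and the other is not. The article does not say this: it plans an interaction test or direct group comparisons. The 2% to 36% in the working shows what that shortcut would risk, not what the plan does.

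Regression to the mean from MAL selection is not needed for the point either. The MAL is taken at screening and again at the evaluation visit.

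Finally, the Mann-Whitney tests are valid under randomisation, so ignoring baseline costs efficiency and does not cause bias. That also stands, and at ρ = 0.5 a comparison of change gains nothing over raw scores.

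**Conclusion.** The point holds in limited form. The sentence that names the effect of the intervention is wrong as written: it attaches the only stated 95% CI to a quantity that cannot separate priming from m-CIMT, practice and time. Neither branch names a between-group difference with a CI. This follows from the text and needs no assumption. It is also not a detail left to a fuller plan, because the article names an estimate and gives it a purpose it cannot serve.

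In the parametric branch the trial's question is still tested properly, so the defect there is one of estimation and reporting. In the nonparametric branch differential change is not tested, baseline is unused and no effect is estimated.

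The sizes rest on the assumed inputs. With no priming effect, the AE arm's interval excludes zero in 76% to 99% of trials. With a 0.5 SD effect, raw Mann-Whitney at 0.05 has 47–48% power, against 62–90% for a baseline-adjusted comparison at the same level. How often the fallback branch will be used cannot be known from the article.

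**What to change.** Replace the sentence on within-group mean differences with one along these lines:

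> The effect of the intervention is the between-group difference (AE + m-CIMT minus Stretching + m-CIMT), adjusted for baseline or in change from baseline, with its 95% CI at 3, 30 and 90 days. Within-group changes are descriptive.

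Baseline adjustment is the better of the two options. Its variance factor 1−ρ² never exceeds that of a raw comparison, whereas change from baseline helps only when ρ is above 0.5.

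In the nonparametric branch, either compare change from baseline between groups (Mann-Whitney on change, with a Hodges-Lehmann shift and its interval), or run the baseline-adjusted analysis with a bootstrap interval or on a transformed outcome. Wilcoxon tests within groups can stay as description. If partial eta squared is kept, say that it refers to the group-by-time interaction.

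The four visits already supply the data, so no extra measurement is needed. The cost is a few lines of text and slightly more analysis work. A transformed outcome also needs care in reporting results back in clinical units.

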## Discussion

One of the most significant difficulties in neurorehabilitation is the recovery of fine upper limb skills [68] after stroke, and most studies did not evaluate manual dexterity and upper limb performance using 3DMA. Aerobic exercise potentiates neuroplasticity and may improve motor recovery after stroke [19, 63]. Performed alone, aerobic exercise can enhance motor function after stroke; motor learning in stroke rehabilitation may improve when aerobic exercise is performed before motor training. This study will investigate, using a randomized clinical trial, whether AE can enhance the effect of m-CIMT on the manual dexterity recovery in the paretic upper limb of people in the chronic phase poststroke.

According to the literature, the deficit in the UE can negatively affect the quality of life of the survivor; that deficit includes voluntary impairment control of finger extension from coactivation and decreased gross and fine manual dexterity. Poor dexterity is associated with the correlation between the ability to use hands and manipulating objects and independence in life activity.

Kinematic analysis can provide objective, quantitative, accuracy measures of arm motor impairment after stroke, with the ability to detect and quantify differences in movement patterns. Furthermore, these data enable the evaluation of the nature of the functional improvement, namely, the determination of whether compensatory strategies or recovery of normal movement are the cause.

This study will provide valuable information about the effect of motor priming for fine upper limb skill improvement in people with chronic poststroke hemiparesis, generating new evidence about the association of therapies highly used on clinical practice.

## Data Availability

Not applicable.

## Abbreviations

AE: Aerobic exercise
BBT: Box and Block Test
FAS: Functional ability scale
HR_reserve_: Reserve heart rate
MAL: Motor Activity Log
m-CIMT: Modified Constraint-Induced Movement Therapy
NAS: Nottingham Assessment Sensory
NHPT: Nine-Hole Peg Test
SS-QOL: Quality of Life Questionnaire
TEFDD-c: Continuous Dynamic Stress Test
UE-FMA: Upper-Limb Fugl-Meyer Assessment
WMFT: Wolf Motor Function Test
